### Early pregnancy

At around 14 weeks gestation women attend the research clinic at Princess Anne Hospital. The timing of this appointment can be later if they are not recruited by 14 weeks. During the appointment, an interviewer-led questionnaire is administered to gather information on parity, baseline demographic features, diet, smoking, alcohol intake, exercise, sunlight exposure, general health, medication, psychological health and wellbeing, self-efficacy and food involvement. Diet is assessed using a 20-item food frequency questionnaire (FFQ) which was developed from a larger FFQ [23]. Data from the FFQ are used to produce a standardised score (with mean 0 and standard deviation 1.0). This score has been named the ‘prudent diet score’. The 20-item FFQ gives closely comparable scores to the full FFQ and can be used in settings where administration of a longer FFQ is not feasible.

For women in the Healthy Conversation Skills intervention group, this appointment also presents an opportunity for the first Healthy Conversation with a trained research nurse. Women are asked about their lifestyle and health behaviours and what they would like to do to ensure they have healthy pregnancies and healthy babies, and to set some goals for achieving this. Details of the conversations and goals are recorded in a Case Report Form and revisited at future appointments.

Women’s height, weight, skinfold thickness (triceps, biceps, subscapular and suprailiac) and grip strength are measured. Venous blood samples are taken and stored with the aim of measuring biomarkers of quality of diet, including beta carotene and vitamin D. With participants’ consent, blood pellets are stored to allow future DNA analysis.

### 18–21 weeks gestation

Women attend at 18–21 weeks for a National Health Service (NHS) fetal anomaly scan and an additional high-resolution 3D ultrasound scan to obtain detailed measurements of their pregnancies. These scans are performed by the SPRING study sonographer. If any abnormalities are identified, women are referred to their local fetal medicine department for further management and might be excluded from this trial if the diagnosis would make it difficult for them to continue either with the IMP or the study procedures. The findings of any abnormal scans will be recorded as adverse events and thus might inform potential new hypotheses regarding the action of vitamin D in pregnancy. A pill count is performed to assess compliance with the study.

During the 18–21 weeks visit, and after the scan, the intervention research nurses hold a second Healthy Conversation with women in the Healthy Conversation Skills intervention groups to discuss their pregnancies, explore progress towards any goals they set at the 14 week visit and to set new ones if need be. Details of conversations are recorded on the Case Report Form. This forms part of the implementation component of process evaluation. Control research nurses give control group women an information sheet and confirm the timing of the 26 week phone call.

### 26 weeks gestation

At 26 weeks gestation, all women taking part in the trial receive a phone call from the research nurses. Healthy Conversation Skills intervention women are phoned by intervention nurses who hold a Healthy Conversation with them and explore progress towards their goals. Women in the normal care control group receive calls from control group nurses. The call is used to check personal details and confirm the time of their next appointment. All calls, to both intervention and control women, are audio-recorded to inform the evaluation of intervention implementation.

### 34 weeks gestation

Women attend the research clinic at 34 weeks gestation for a repeat growth and 3D ultrasound scan, questionnaire and blood tests. Those in the Healthy Conversation Skills intervention group have a Healthy Conversation with an intervention research nurse to monitor their goals and offer support. Women in the control group have contact with control group nurses and receive standard antenatal care. Questionnaires administered at this visit assess intake of foods and supplements containing vitamin D, smoking, alcohol, exercise, medications, health, well-being and self-efficacy. Venous blood samples taken at this visit are used to measure 25(OH) vitamin D, calcium, alkaline phosphatase, albumin and dietary biomarkers such as beta carotene and vitamin C. Any woman found to be hypercalcaemic (serum calcium >2.75 mmol/l) is followed up and managed appropriately. Compliance with the study medication is assessed by pill count. Mothers are given an information sheet about the neonatal DXA scan at this visit.

### Admission to hospital for labour

The study co-ordinator/research nurse is informed of any women entering labour by the NHS midwives or by the women themselves or their partners. The attending midwives collect venous umbilical cord blood (including samples for genetic analyses) and placental and umbilical cord tissue samples at delivery. The tissue samples will allow exploration of the effect of vitamin D supplementation on calcium transport across the placenta. After ensuring the infant’s hips have been assessed by a paediatrician to exclude congenital hip dislocation, a research nurse measures the baby’s length, weight, skinfolds and abdominal circumference, and arranges an appropriate time for the baby to undergo bone density assessment by DXA.

### Neonatal DXA

Infants receive DXA scans within the first 2 weeks after delivery. The reliability of DXA measurements in neonates has been demonstrated in the Southampton Women’s Survey [2]. The baby is pacified, fed, fully undressed and then swaddled in a towel before being placed on the densitometer (Hologic Discovery instrument using paediatric software (Hologic Inc., Bedford, MA, USA)). The scanner is calibrated against a spine phantom every day together with daily quality assurance and step-wedge calibration, performed as per manufacturer’s instructions (Hologic Inc., Bedford, MA, USA). If possible, the baby is scanned while still an inpatient. If this is not possible, the mother and baby return for assessment within 14 days of birth. Whole body and lumbar spine bone area, bone mineral content and bone mineral density are measured. The infant DXA assessments are associated with a low dose of radiation exposure, roughly equivalent to 2 days of background radiation in Cornwall (UK) and 7 days in other parts of the UK.

### One month after birth

Mothers and their babies are visited at home by an intervention or control nurse, depending on their allocation to Healthy Conversation Skills. Questionnaires are administered repeating the questions used at 34 weeks but also asking questions about infant feeding in order to establish whether breastfeeding has been initiated and is maintained. Mothers in the Healthy Conversation Skills intervention group also have a Healthy Conversation with a research nurse during which the mother’s goals for herself and her baby are reviewed. As before, the content of the conversation is recorded. All mothers are asked whether they consent to be contacted in the future if the study receives funding for a follow-up during childhood.

### Inclusion and exclusion criteria

#### Inclusion criteria

The inclusion criteria are as follows:Less than 17 weeks gestation at recruitment based on last menstrual period (LMP)Aged over 18 yearsSingleton pregnancyAiming to give birth at local maternity (Princess Anne) hospital.

#### Exclusion criteria

The exclusion criteria are as follows:Known metabolic disease or chronic disease associated with bone metabolismCurrent medication likely to interfere with intrauterine growthInability to give informed consentHistory of renal stores, hyperparathyroidism or hypercalciuriaA diagnosis of cancer in the last 10 yearsSerum calcium >2.75 mmol/l.

### Timing of pregnancy

Many women do not know the exact timing of conception. Thus, gestation based on the timing of a woman’s last menstrual period (LMP) and that based on ultrasound scan often differ. Therefore, women coming for their dating scan between 8 and 12 weeks might find they are actually a few weeks earlier or later in their gestation than they thought. All assessments will be performed as closely as possible to the gestational timing outlined in the protocol. Where this is not possible, the following limits will be observed:Women with gestations between 8 and 17 weeks can be included in the trialDating scans take place between 8 and 12 weeksNuchal translucency scans cannot be performed before 11 weeks, and so women with pregnancies of earlier gestation might be asked to return at 11 or 12 weeksEarly pregnancy visits will be performed as closely as possible to that time but will be acceptable until the anomaly scan at 18–21 weeksThe anomaly scan is performed between 18 and 21 weeksThe 34 week scan will be performed between 33 and 36 weeks but, if delayed, can be performed up to delivery

### Sample size and power calculation

Our power calculation uses an alpha of 0.025 taking into account the two primary outcomes of maternal vitamin D and maternal diet quality. With 150 participants in each arm of the trial (equivalent to 300 participants per arm in each comparison between HCS and routine care and between vitamin D and placebo) there is 80 % power at an alpha of 0.025 to detect a 0.25 standard deviation difference in both diet quality score and vitamin D (approximately 3 nmol/l 25(OH)) between groups. Allowing for a 20 % drop-out rate, we aim to recruit 188 women to each arm of the four arms of the trial in order to achieve 150 women in each arm. Pilot data suggest that around 40 % of women who are approached will agree to participate in the study, and so initial invitations will be issued to 1250 women. Experience in the MAVIDOS trial indicates that women will be recruited at a rate of 5–8 per week, suggesting that recruitment will take up to 3 years.

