## Background

The nutritional status and health of mothers influence the growth and development of infants during pregnancy and postnatal life [1]. Growth and development at these stages of the lifecourse will influence the risk of non-communicable diseases such as cardiovascular disease and obesity in adulthood. Interventions that focus on improving the nutritional status and lifestyle of mothers have the potential to optimise the growth and development of the fetus as well as improve the health of mothers themselves. Studies have shown that maternal nutrition influences child body composition [2, 3]. There are two principal approaches to improving the nutritional status of pregnant women: nutritional supplementation (multiple-micronutrient supplementation as well as single vitamin supplements to correct deficiencies) or behaviour change interventions that aim to improve the diet quality of pregnant women [4]. Improving the diets of women of childbearing age is likely to require complex interventions that are delivered in a socially and culturally appropriate context [5].

Multiple-micronutrient approaches have improved maternal and birth outcomes in studies of pregnant women in developing countries [6]. In Mumbai, India, for example, a food-based multiple-micronutrient supplement started preconceptionally and given throughout pregnancy halved the prevalence of maternal gestational diabetes [7]. Correction of specific vitamin deficiencies during pregnancy has improved outcomes for pregnant women and their babies in developed and developing country settings [8]. In a recent UK multi-centre trial of vitamin D supplementation during pregnancy, the Maternal Vitamin D Osteoporosis Study (MAVIDOS), supplementation corrected maternal vitamin D deficiency and optimised infant levels of vitamin D [9, 10].

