### Primary outcomes

Given the factorial design of the trial, there are two primary outcomes:Maternal circulating plasma 25(OH) vitamin D concentration at 34 weeksMaternal diet quality at 34 weeks gestation assessed with a 20-item food frequency questionnaire [23]

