### Vitamin D supplementation

Vitamin D supplementation consists of a daily oral supplement of 1000 IU cholecalciferol. Each woman receives a single box of blister-packed capsules of vitamin D or placebo to last for the duration of her pregnancy. Each pack is individually prescribed for each participant. The trial’s pharmacist allocates a pack to that prescription, documenting both the pack number and the SPRING participant’s unique ID number. These are checked again by the research nurse, who collects them from pharmacy ready to issue to participants at the 14 week visit, and documented in the participant’s notes. The medication comes with a tear-off adhesive label which is placed in the notes as an added safeguard against error in pack allocation. A sticker is applied to the obstetric notes of women taking part in the trial in order to alert clinicians to their enrolment. An information sheet and copy of the consent form are filed in each woman’s notes. The mother (with a copy to the father) is given contact details for the study co-ordinator and research nurse and asked to inform them immediately when labour begins.

The Investigational Medicinal Product (IMP) and matched placebo are manufactured by Sharp Clinical Services (UK) Ltd, [name]. The manufacturer has no role in the trial other than supply of the randomised IMP. As with the MAVIDOS trial, the IMP capsules contain 1000 international units (IU) of cholecalciferol (vitamin D3, supplied by Merck KGaA, Darmstadt, Germany, who also had no other role in the trial), with excipients matched to the placebo capsule [9]. Study medication (active/placebo) is supplied to the local pharmacy pre-randomised 1:1 by the manufacturer, using a computer system, and sequentially numbered for storage and dispensing. Code-break envelopes are supplied to the lead pharmacist but are not available to the investigative team. Emergency code-break access is available through the principal investigator and on-call pharmacist.

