### Statistical analyses

We will perform a complete case analysis for each outcome using *t* tests to compare the two primary outcomes between the relevant intervention arms. Multiple linear regression will be used to adjust for any differences identified at baseline. Similar analyses will be conducted for the secondary outcomes. The neonatal bone and body composition analyses will include stratification by season of birth in light of recent findings from the MAVIDOS trial [10]. We will also conduct exploratory analyses of the interaction between HCS and vitamin D on both primary outcomes. For binary outcomes, chi-squared tests or Fisher’s exact test for rare outcomes will be used. To adjust for imbalances at baseline, logistic regression will be used, or for rare outcomes, binary regression or Poisson regression with robust variance.

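### Cheap improvement, not an error: Holm's step-down test in place of a fixed 0.025 per primary outcome would raise power for diet quality from 79.2% to about 85% at the same 5% overall error

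*Protocol article*

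**What the plan says.** The section on primary outcomes names two, 25(OH) vitamin D concentration and diet quality score, both at 34 weeks: "Given the factorial design of the trial, there are two primary outcomes". The sample size section deals with multiplicity in one sentence: "Our power calculation uses an alpha of 0.025 taking into account the two primary outcomes of maternal vitamin D and maternal diet quality". It then claims 80% "power at an alpha of 0.025 to detect a 0.25 standard deviation difference in both diet quality score and vitamin D", with 150 analysed in each of the four groups, "equivalent to 300 participants per arm in each comparison between HCS and routine care and between vitamin D and placebo".

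The section on statistical analyses plans t "tests to compare the two primary outcomes between the relevant intervention arms". It states no significance level, step-down rule or order of testing. The 0.025 in the sample size section is therefore the only multiplicity provision in the document.

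Two further places bear on how likely the vitamin D test is to reject. The Background says that in an earlier UK multi-centre trial "supplementation corrected maternal vitamin D deficiency and optimised infant levels of vitamin D". The section on supplementation says "As with the MAVIDOS trial, the IMP capsules contain 1000 international units (IU) of cholecalciferol". On the behavioural side, the Background reports that the team's earlier programme had a protective effect on women's sense of control and self-efficacy, but that no influence on diet was seen.

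**The concern.** By sizing each outcome at 0.025, the sponsor has chosen to control error across the two primary outcomes together. If the same 0.025 is used as a fixed threshold in the analysis, that is a Bonferroni split. With two tests, Holm's procedure rejects everything the split rejects and sometimes more, at the same familywise error.

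The difference falls where this trial can use it. On the document's own account, vitamin D is the outcome with the better prior support and diet quality the less certain one. Under a fixed split, a clear vitamin D result does nothing for diet quality, and a diet p-value between 0.025 and 0.05 counts as not significant. Under Holm, rejecting the vitamin D null frees the full 0.05 for diet quality. What is at stake is several points of power on one of the two primary questions, available without recruiting anyone.

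**Working it through.** **Inputs.** From the sample size section: 300 v 300 in each factorial comparison, effect 0.25 SD on both outcomes, alpha 0.025 per outcome, 20% drop-out. The diet score is scaled to SD 1 (section on early pregnancy: "Data from the FFQ are used to produce a standardised score (with mean 0 and standard deviation 1.0"). Sidedness is not stated.

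**1. Reproduce the stated power.** Noncentrality = 0.25 × √(300/2) = 0.25 × 12.247 = 3.062.
- Two-sided 0.025, normal approximation: Φ(3.062 − 2.241) = Φ(0.821) = 79.4%. Non-central t with 598 df: 79.2%. This agrees with the stated 80%.
- One-sided 0.025 gives 86.4%, which does not agree, so 0.025 is read as two-sided.

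**2. Power at the full 0.05.** Normal: Φ(3.062 − 1.960) = Φ(1.102) = 86.5%. Non-central t: 86.4%. The t figures, 0.7922 and 0.8637, are used below.

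**3. Diet-quality power under Holm.** The diet null is rejected if its p ≤ 0.025, or if its p lies between 0.025 and 0.05 and the vitamin D p ≤ 0.025. In a balanced 2×2 factorial the two main-effect contrasts are orthogonal, so the tests are treated as independent:

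power = P(0.025) + [P(0.05) − P(0.025)] × q, where q is the power of the vitamin D test at 0.025.

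The bracket is 0.8637 − 0.7922 = 0.0715.

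| Vitamin D effect | q | Diet power under Holm | Gain over 79.2% |
|---|---|---|---|
| none | 0.025 | 0.7922 + 0.0715 × 0.025 = 79.4% | 0.2 points |
| 0.25 SD (the plan's assumption) | 0.7922 | 0.7922 + 0.0715 × 0.7922 = 84.9% | 5.7 points |
| rejection nearly certain | 1 | 0.7922 + 0.0715 = 86.4% | about 7.1 points |

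A simulation with 2 million replicates, using normal test statistics, agrees: 85.1% in the second case and 86.5% in the third. If the two test statistics had a correlation of 0.3 (an assumption), the second case would be 84.4%.

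**4. Familywise error under Holm.** With both nulls true, an error needs the smaller p ≤ 0.025: 1 − 0.975² = 4.94% (simulated 4.95%). With only the diet null true and vitamin D certain to be rejected, the simulated error is 5.0%.

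**5. What the gain is worth in women.** To reach 86.4% with a fixed 0.025 (normal approximation): n = 2 × (2.241 + 1.098)² / 0.25² ≈ 357 per side. That is 57 more per side and 114 in all. At 20% drop-out it is 114 / 0.8 ≈ 143 more recruited. This is the equivalent of the largest gain in the table.

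**6. Chance of success on both outcomes at the planned effects.** Fixed split: 0.7922² = 62.8%. Holm: 0.8637² − 0.0715² = 74.1%.

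**The case against.** **The document does not fix the rule.** The 0.025 is a sizing assumption, and the analysis section sets no test level. An analysis plan not available here could specify Holm already, and sizing at 0.025 is compatible with Holm, whose first step is 0.025. This stands. The loss is conditional on 0.025 being used as a fixed test level, and the power statement itself needs no correction.

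**A Bonferroni split is valid, and linking the tests is a choice.** The trial is presented as testing each intervention separately. Under Holm, the verdict on Healthy Conversation Skills for a diet p between 0.025 and 0.05 depends on the vitamin D result. A trialist may dislike that. It is a matter of taste, though: each intervention is still judged on its own comparison, and the link can only add a rejection.

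**The intervals fit less well.** This also stands. When diet p lies between 0.025 and 0.05 and Holm rejects, a 97.5% interval includes zero, so every rejection that Holm adds would sit beside a 97.5% interval that appears to contradict it.

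**The gain is conditional.** It is about 0.2 points if vitamin D has no effect. The document's account of the earlier trial at the same capsule strength makes that case unlikely but does not exclude it.

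A reader might also infer that, because the analysis section is silent, both outcomes will be tested at 0.05 and the overall error will be inflated. The documents do not support this. The only level they mention is 0.025, and the full inflation would also require both null hypotheses to be true.

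**Conclusion.** The point holds as a low-cost improvement. It is not a finding of error: the stated 80% power is correct, and a fixed 0.025 per outcome controls the overall error. Nor does the document show that the sponsor has committed to testing diet quality at a fixed 0.025. A reader might infer that from the sample size section, but the analysis section leaves the level open.

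If 0.025 is carried into the tests, Holm adds 5.7 points of power for diet quality under the plan's own assumption of 0.25 SD on both outcomes. It adds about 7.1 points at most, about 0.2 if vitamin D has no effect, and never takes any away. These figures rest on two-sided tests, 300 analysed per side, a true diet effect of 0.25 SD and independent contrasts. Once the sponsor has chosen to control error across the two outcomes, the only argument left for the fixed split is simpler reporting.

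**What to change.** Add to the section on statistical analyses (or to the analysis plan, if it does not already say so), before unblinding: the two primary outcomes are tested by Holm's procedure at an overall two-sided 5%; the smaller p-value is compared with 0.025 and, if it rejects, the other with 0.05.

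Keep the 0.025 power statement in the sample size section as the worst case. If wanted, add that diet-quality power under Holm is about 85% at the planned effects.

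Report 95% intervals for both outcomes, with 97.5% intervals alongside if wanted. State in advance that the Holm decision, and not whether an interval excludes zero, determines significance.

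The cost is a sentence or two of text and slightly less simple intervals. No extra women, visits or data are needed.

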### Statistical analyses

We will perform a complete case analysis for each outcome using *t* tests to compare the two primary outcomes between the relevant intervention arms. Multiple linear regression will be used to adjust for any differences identified at baseline. Similar analyses will be conducted for the secondary outcomes. The neonatal bone and body composition analyses will include stratification by season of birth in light of recent findings from the MAVIDOS trial [10]. We will also conduct exploratory analyses of the interaction between HCS and vitamin D on both primary outcomes. For binary outcomes, chi-squared tests or Fisher’s exact test for rare outcomes will be used. To adjust for imbalances at baseline, logistic regression will be used, or for rare outcomes, binary regression or Poisson regression with robust variance.

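### The primary analysis is an unadjusted complete-case t test, with adjustment only for baseline differences that happen to be seen. With 20% loss allowed for and possible exclusions after an abnormal scan, this weakens the protection of randomisation, mainly for diet quality.

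*Protocol article*

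**What the plan says.** The Statistical analyses section of the protocol article fixes the method for the two primary outcomes (25(OH) vitamin D and diet quality at 34 weeks): "We will perform a complete case analysis for each outcome using" t tests between the relevant arms. The next sentence adds: "Multiple linear regression will be used to adjust for any differences identified at baseline".

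The Sample size section allows for 20% loss: "drop-out rate, we aim to recruit 188 women to each arm of the four arms of the trial", so that 150 remain in each.

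The section on 18–21 weeks gestation says that women with an abnormal scan "might be excluded from this trial if the diagnosis would make it difficult for them to continue" with the capsules or the study procedures. It adds that such findings could suggest hypotheses about what vitamin D does in pregnancy. The Vitamin D supplementation section has packs issued at the 14 week visit, so this exclusion normally comes after treatment has started.

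On blinding, the Study design and Randomisation sections make the vitamin D factor blind to women and research team. Staff know the Healthy Conversation Skills (HCS) allocation, and separate groups of three nurses see the two HCS arms.

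**The concern.** Raising recruitment from 150 to 188 per cell restores precision. It does nothing about who is lost. A complete-case difference departs from the difference between the groups as randomised when loss is related to outcome and that relation, or the amount of loss, differs between arms.

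The article gives a plausible route for diet quality. It links low self-efficacy to poor diet. HCS women set goals that are reviewed at each visit, control women do not, and different nurses see each group. Women who struggle with diet could therefore leave one arm at a different rate from the other.

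The planned adjustment does not address this. Covariates enter because an imbalance was noticed, not because they predict the outcome or the loss. Yet the Early pregnancy section already provides the baseline value of each primary outcome: the same 20-item FFQ, and a stored blood sample intended for vitamin D among other markers.

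The scan exclusion adds a second, smaller route. It depends on a finding made after allocation, and the text does not separate stopping capsules or procedures from leaving follow-up and analysis.

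**Working it through.** **1. The plan's own figures.** Inputs from the Sample size section: "Our power calculation uses an alpha of 0.025 taking into account the two primary outcomes"; 80% "power at an alpha of 0.025 to detect a 0.25 standard deviation difference in both diet quality score and vitamin D"; "equivalent to 300 participants per arm in each comparison between HCS and routine care and between vitamin D and placebo". Sidedness is not stated; two-sided reproduces the figure.

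- Standard error = √(2/300) = 0.0816 SD; 0.25/0.0816 = 3.062.
- Power = Φ(3.062 − 2.241) = 0.794, against 80% stated. The one-sided version gives 0.865 and does not match.
- Recruitment: 150/0.80 = 187.5, so 188 per cell; 4 × 188 = 752 in all, 376 per comparison arm; 752 − 600 = 152 lost.

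The sample size stands, and the 20% is already in it.

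**2. Bias of a complete-case difference.** Let p be the fraction missing in an arm and g the mean of observed women minus the mean of missing women, in SD. The full-arm mean is (1 − p) × observed + p × missing, so observed minus full equals p × g. Hence

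bias b = p₁g₁ − p₀g₀.

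**3. Effect on error rates.** With 376 randomised per comparison arm, SE = √(1/[376(1 − p₁)] + 1/[376(1 − p₀)]) and z = 2.241:

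- type I error = 1 − Φ(z − b/SE) + Φ(−z − b/SE)
- power, if the bias is towards the null ≈ Φ((0.25 − b)/SE − z)

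The documents give only the 20% overall. The loss per arm and the gaps below are assumptions.

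| Loss, arm 1 v arm 0 | Gap, arm 1 v arm 0 (SD) | Bias (SD) | Share of 0.25 SD | Type I error | Power if bias is towards null |
|---|---|---|---|---|---|
| 20% v 20% | 0.5 v 0.5 | 0 | 0 | 0.025 | 0.795 |
| 22% v 18% | 0.5 v 0.5 | 0.02 | 8% | 0.029 | 0.718 |
| 25% v 15% | 0.5 v 0.5 | 0.05 | 20% | 0.054 | 0.582 |
| 20% v 20% | 0.5 v 0 | 0.10 | 40% | 0.155 | 0.344 |

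Example, third row: b = 0.25 × 0.5 − 0.15 × 0.5 = 0.05; SE = √(1/282 + 1/319.6) = 0.0817; b/SE = 0.61; type I error = 0.054.

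The first row shows that outcome-related loss alone need not bias the difference. The last is an extreme case, kept to show that equal drop-out rates are no guarantee.

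For scale, the article equates 0.25 SD with about 3 nmol/l, so 1 SD is about 12 nmol/l. A bias of 0.05 SD would be 0.6 nmol/l if such inputs applied to 25(OH)D.

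**4. Scan exclusions alone.** No rate is given. Assume 1–2% of 752 (8 to 15 women), all in one comparison arm (2–4% of it) and differing by 0.5 SD. Then b = 0.02 × 0.5 to 0.04 × 0.5 = 0.01 to 0.02 SD, with every exclusion placed in one arm.

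**The case against.** Four stronger readings are tempting, and the article does not support them.

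- **That the randomised comparison is broken, or that the test is valid only if data are missing completely at random.** Women are still compared by allocated arm, and nothing in the analysis section drops non-compliers. The difference is unbiased if loss is unrelated to outcome within arm, or if loss times gap is equal in the arms.
- **That both primary results are equally exposed.** The goal-setting route concerns diet quality. For 25(OH)D, allocation is double blind, and the only specific route is the scan exclusion, which is small.
- **That scan exclusion is a treatment effect removing many women.** The wording is conditional, no rate is given, such women may already be within the 20%, and the findings are recorded as adverse events. Suggesting a hypothesis is less than stating an effect.
- **That the lack of a named intention-to-treat set or missing-data sensitivity analysis is itself an error.** These may stand in the full protocol or SAP, which are not shown.

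Other text also limits differential loss under HCS: women are not told what the intervention entails, both groups have the same number of contacts, and retention is monitored. Regression is planned in some form. For a single 34 week outcome, regression on baseline covariates already handles loss that depends on those covariates, so multiple imputation from the same data would add little as the primary analysis.

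All of this stands. What remains is that the article names its primary method, so the point is not an omission left to the SAP. The method leaves the baseline values out unless an imbalance happens to be seen.

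**Conclusion.** The point holds in limited form and should be acted on. The stated primary analysis gives less protection against selective loss than data already collected would allow, and the scan wording leaves unclear whether affected women remain in follow-up. Bias is possible, not shown. On the assumed inputs a reasonable range is 0 to 0.05 SD, up to a fifth of the target difference, with type I error between 0.025 and 0.054. Larger values need gaps that differ sharply between arms. The concern is greater for diet quality than for 25(OH)D, and scan exclusions add about 0.02 SD or less at the assumed rates.

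**What to change.** 1. **Primary analysis.** Replace the t test and imbalance-driven adjustment by a prespecified linear regression of each 34 week primary outcome on allocated group, its own baseline value (14 week FFQ score; 25(OH)D assayed from the stored early-pregnancy sample) and a few named predictors of loss, analysing all women by allocation. This also gains precision, by an amount that depends on the baseline-to-34-week correlation, which the article does not give.
2. **Sensitivity analysis.** Add multiple imputation with a delta shift for unobserved outcomes, restricted to women still pregnant at the 34 week assessment. The article anticipates miscarriage, stillbirth and premature delivery; a 34 week value is undefined once the pregnancy has ended.
3. **Reporting.** Give losses and scan exclusions by arm and reason.
4. **18–21 weeks section.** Separate stopping capsules or procedures from leaving the trial, so that these women stay in follow-up where they consent and in the analysis set. Clinical decisions are left as they are.

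Cost: assay of baseline samples already stored, modest extra analysis, and a little effort to seek outcomes in a few women. The sample size does not change.
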